#### 2.9.2. Qualitative evaluation.

All the semi-structured interviews will be transcribed (verbatim), translated to English (if necessary), anonymized, and checked for accuracy. For transcription and translation, encrypted files will be transferred to an external transcription and translation company after signing the non-disclosure agreement. An interpretive analysis will be conducted using thematic analysis,^[35]^ using NVivo software (2020). Transcripts will be read and re-read. Initial codes will be developed and applied initially to a small number of transcripts, enabling further iteration of the thematic index which will then be applied and refined across all the transcripts. We will use illustrative non-attributable quotations.

### 2.10. Sample size

#### 2.10.1. Cluster RCT.

A formal sample size calculation is not usually required for a feasibility trial, and it is recommended to recruit at least 50 participants in a feasibility trial.^[36]^ After taking into account the cluster study design and loss to follow-up, we will recruit at least 120 participants (60/group) in this feasibility cluster RCT to estimate the SD of the primary outcome measure (i.e., HbA1c level at 6-month follow-up). This sample size is calculated in relation to the desired level of confidence (95%) for the SD, the chosen power (80%) and significance level (5%, 2-tailed), and the expected loss to follow-up (20% at 6 months), intraclass correlation coefficient (0.03), and mean cluster size (10 participants).^[36–38]^

#### 2.10.2. Qualitative evaluation

Interviews will be conducted with around 20 to 30 participants. Until data saturation is achieved, purposive sampling will be used for ensuring the representation of diversity within the cluster RCT population.^[35]^Interviews will be conducted with around 10 to 15 people (continue until data saturation is reached) who decline to participate in the study but agree to be interviewed about their reasons for nonparticipation.^[35]^Interviews will be conducted with all the participating ayurvedic practitioners (continue until data saturation is reached).^[35]^

### 2.11. Ethics and other related issues

Ethics approval has been obtained from the following: Research Ethics Committee, Faculty of Medicine and Health Sciences, University of Nottingham, UK (511-2003) and Ethical Review Board, Nepal Health Research Council, Nepal (66/2022). The clinical trial license has been received from the Department of Drug Administration, Nepal. An independent Trial Steering Committee, consisting of relevant experts, is monitoring and providing overall supervision for the study.

### 2.12. Adverse events and serious adverse events

Information will be collected on adverse events and serious adverse events (including death) occurring in participants. Based on medical and scientific judgment, an independent clinician (diabetologist) will determine the relationship of any serious adverse event to the interventions.

### 2.13. Participant withdrawal

Participants will be withdrawn from the study either at their request or at the discretion of the site investigator (e.g., if a female participant gets pregnant during the study period, if a participant develops a serious or uncontrolled medical condition (e.g., cancer) during the study period). Participants will be made aware that this will not affect their future care. Also, they will be made aware (via the participant information sheet and consent form) that should they withdraw, the data collected to date will not be erased and may still be used in the final analyses.

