### 2.3. Randomization and blinding

Ayurveda centers are randomized to the intervention or control group according to a computer-generated randomization schedule (1:1 using Random Allocation Software Version 1.0), performed by an independent statistician at the Nepal Health Research Council, Kathmandu, Nepal. Ayurvedic practitioners and participants cannot be “blinded” to group allocation, but the outcome assessors are “blind”. The outcome assessors are an independent team of trained researchers. To give some protection against contamination, intervention group ayurvedic practitioners have signed a nondisclosure form, and they are not allowed to disclose the content of the intervention to anyone.

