### 2.8. Study parameters and data collection

#### 2.8.1. Cluster RCT

For sample size calculation of the definitive cluster RCT:The standard deviation (SD) of the primary outcome measure (i.e., HbA1c level at 6-month follow-up).Another estimate of intraclass correlation coefficient and cluster size (i.e., the number of participants recruited per ayurveda center during the recruitment period).Recruitment: The number of people approached to participate, written informed consent given, screened for eligibility, found eligible, and recruited.The time needed to recruit participants.Follow-up: The number of participants followed up for 6 months.Adherence: In the intervention group, the number of participants adhering to the recommended ayurvedic medicine (assessed using a self-reported diary and by medicine counting at the sites).Others: See Table 1.

A standard operating procedure is developed and used for data collection. Blood and urine samples are collected and analyzed at local laboratories, accredited by the National Public Health Laboratory in Nepal.

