### 2.9. Data analyses

#### 2.9.1. Cluster RCT.

We will summarize the data using numbers and percentages for categorical data and summary measures of mean or median and spread for continuous data. Being a feasibility cluster RCT, it is not adequately powered to detect a difference in trial outcomes between the 2 arms. However, unadjusted mean difference or odds ratio with 95% CI will be reported to indicate initial estimates of effects. Subsequently, for critical outcomes like HbA1c, ANCOVA analysis will be conducted, allowing for clustering and adjustments made for the individual’s baseline value and subsequently, also for the individual’s age and sex and cluster (ayurveda center) mean.^[34]^ The regression coefficient and 95% CI will be reported. All analyses will be based on the intention-to-treat principle. Being a short-term feasibility study, no interim analysis is planned. STATA V.17 will be used for data analyses.

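### Investigators may withdraw participants from the study itself, with no stated provision for the 6-month HbA1c afterwards; this sits badly with the intention-to-treat statement and blurs the retention estimate

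*Protocol article*

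**What the plan says.** Section 2.13 of the protocol article sets the rule: "Participants will be withdrawn from the study either at their request or at the discretion of the site investigator". Its examples of investigator withdrawal are pregnancy and the case "if a participant develops a serious or uncontrolled medical condition (e.g., cancer) during the study period". These are examples, so the list is open, and they mirror two of the baseline exclusions in section 2.6.2. Participants are told that, should they withdraw, "the data collected to date will not be erased and may still be used in the final analyses".

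Section 2.9.1 states: "All analyses will be based on the intention-to-treat principle".

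On blinding, section 2.3 says "Ayurvedic practitioners and participants cannot be “blinded” to group allocation". Of those who measure outcomes, whom it describes as blind, it says: "The outcome assessors are an independent team of trained researchers". It does not say which group the site investigator belongs to.

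Section 2.8.1 lists the parameters wanted for the definitive trial. They include the SD of HbA1c at 6 months, the intraclass correlation, and follow-up, defined as "The number of participants followed up for 6 months". Section 2.10.1 allows for 20% loss at 6 months among at least 120 participants. The Discussion names follow-up among the criteria for judging whether the definitive trial is feasible.

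**The concern.** The rule makes no distinction between ending study management and ending observation. If it is followed as written, a participant who develops a qualifying condition leaves the study, keeps only the measurements already made, and has no 6-month HbA1c. That person also counts as not followed up. Intention-to-treat is best served by measuring the outcome on everyone in their allocated arm, whatever happens to them later. A rule that ends measurement because of the participant's course works against it.

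Two features make this more than tidiness. First, the decision is discretionary and may rest with staff who know the allocation. Second, the arms could differ in how often a qualifying condition comes to light: section 2.4 says that the guideline covers screening for complications and specialist referral, while section 2.5 leaves control practitioners to usual management.

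At stake are the quantities the trial exists to produce: the retention rate and the SD of 6-month HbA1c. The arm comparison is a lesser stake. Adverse events that follow a new serious condition could also go unrecorded if observation stops at withdrawal.

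**Working it through.** **1. The two rules side by side.** Section 2.13 ends study participation and says that data to date may be used, which permits their use but does not require it. Section 2.9.1 requires intention-to-treat throughout. Both can be obeyed formally: a withdrawn participant can stay in the allocated arm with a missing 6-month value. In the planned ANCOVA of HbA1c, however, a participant without a 6-month value adds nothing unless the missing outcome is handled in some way. The tension is therefore about data that are never collected, not about an instruction to exclude anyone.

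**2. Retention.** Inputs: 120 participants and 20% loss (section 2.10.1). The plan's own expectation is 120 × 0.80 = 96 followed up, or 80.0%. Each further withdrawal costs 1/120 = 0.83 percentage points:

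- 1 more: 95/120 = 79.2%
- 3 more: 93/120 = 77.5%
- 6 more: 90/120 = 75.0%
- 12 more: 84/120 = 70.0%

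The withdrawal counts are assumptions. If the 20% already includes such cases, the total is unchanged, but the mixing of reasons remains. (The 120 itself cannot be rebuilt from the stated inputs. The recommended minimum of 50 with design effect 1 + 9 × 0.03 = 1.27 and 20% loss gives 50 × 1.27/0.8 = 79.4, so 80. The base number behind the SD-precision method is not given, so this supports no verdict, and nothing here depends on it.)

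**3. SD and arm difference, extreme case.** Assume that 6-month HbA1c is normal and that those withdrawn are exactly the highest fraction f. With b the (1 − f) normal quantile and λ = φ(b)/(1 − f), the mean of those remaining falls by λ SD and the variance ratio is v = 1 − bλ − λ². For f = 5%: b = 1.645, λ = 0.1086, v = 1 − 0.1786 − 0.0118 = 0.810, and the SD ratio is √0.810 = 0.900.

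A definitive trial planned on the understated variance gets v times the participants it needs. If it aims for 80% power at two-sided 5% (assumed to match section 2.10.1), its actual power is Φ(2.8016√v − 1.960).

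| Highest fraction lost | SD ratio | Variance (and N) ratio | Actual power | Mean shift if in one arm only |
|---|---|---|---|---|
| 1% | 0.968 | 0.94 | 77% | 0.03 SD |
| 2.5% | 0.938 | 0.88 | 75% | 0.06 SD |
| 5% | 0.900 | 0.81 | 71% | 0.11 SD |
| 10% | 0.844 | 0.71 | 66% | 0.195 SD |

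**4. The other end of the range.** If withdrawal is unrelated to HbA1c, neither the SD nor the arm difference is biased and only precision is lost. For scale, with 96 completers the 95% interval for the SD already runs from 0.876 to 1.166 times the estimate, before clustering.

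**The case against.** Three stronger readings are tempting, and the document supports none of them.

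A reader might infer that the withdrawal rule flatly contradicts intention-to-treat. It does not. Nobody is taken out of the analysis set or the allocated arm, collected data are kept, and handling of missing outcomes is commonly left to a statistical analysis plan, which is not shown here.

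A reader might infer that the site investigator is unblinded. Section 2.3 names only practitioners and participants as unblinded. At an ayurveda centre the inference is plausible, but it remains an inference.

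A reader might infer that poorly controlled diabetes is itself a trigger, so that the highest HbA1c values are removed. The example given is cancer, next to pregnancy. Almost the same words appear as a baseline exclusion in section 2.6.2, in a population that by definition has untreated diabetes. The natural meaning is a new, supervening condition. The open list makes a glycaemic withdrawal possible, but nothing names it.

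Other points also stand. The numbers withdrawn over 6 months are likely to be few. The 20% allowance may already cover them. A 3-month HbA1c (Table 1, footnote) is kept if already taken. Section 2.12 sets no cut-off for adverse event collection. The arm comparison is declared underpowered and serves only as an early indication.

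What survives is the stated rule itself. It withdraws people from the study, and the only data it speaks of are those already collected. That is a rule as written, not a detail left out for brevity.

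**Conclusion.** The point holds as a tension between sections 2.13 and 2.9.1, of moderate to low severity and cheap to put right. Two consequences follow directly from the text. No 6-month HbA1c is provided for after investigator withdrawal, and the follow-up count as defined mixes removal by the investigator with participant drop-out, at 0.83 percentage points per person.

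Bias is possible but not shown. For the SD, withdrawal would have to be related to HbA1c; for the arm difference, that relation would in general have to differ by arm. The SD reductions of about 3% to 16% belong to an assumed extreme mechanism at assumed rates of 1% to 10%. They mark an outer limit at those rates, not an expectation, and the opposite limit is no bias at all.

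**What to change.** Reconcile sections 2.13 and 2.9.1 with these changes:

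- Separate stopping study management from leaving the study. The first stays with the clinician, and no view is taken here on when it should happen.
- Collect the 6-month HbA1c and adverse events for every recruited participant unless that participant withdraws consent for data collection.
- Analyse all participants in the arm to which their centre was allocated, and say that data collected before withdrawal will be used, not that they may be.
- Report investigator-initiated withdrawals by arm and with reasons, separately from loss to follow-up, so that the retention figure carried into the definitive trial has a clear meaning.

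The cost is protocol and site wording, matching text in the participant information sheet and consent form, and one 6-month contact and blood sample for the few participants concerned. Since recruitment began in July 2022, the change helps only those whose 6-month visit is still to come. For anyone already withdrawn, the reason and date can still be reported by arm where they were recorded.

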### 2.14. Dissemination

The findings will be reported according to the relevant extension of the Consolidated Standards of Reporting Trials Statement (i.e., for randomized pilot and feasibility trials).^[39]^ The findings will be widely disseminated among key stakeholders through various avenues, such as through dissemination meetings and informal discussions with them, presentations at national and international conferences, publications in peer-reviewed open-access journals, and press offices and websites of host institutions.

## 3. Discussion

We are now conducting a feasibility cluster RCT in Nepal to determine the feasibility of undertaking the definitive cluster trial. The first participant was recruited on 17 July 2022. If the feasibility is promising (such as recruitment, follow-up, and adherence to the recommended ayurvedic medicine), then the parameters estimated will be used to design the definitive cluster trial. Decisions over whether to modify the protocol will mainly be informed by the qualitative data. We intend to do long-term (≥1 yr) follow-ups in the definitive cluster RCT.

If the intervention is found to be effective in the definitive cluster RCT, people with T2DM in Nepal will benefit from improved health outcomes, such as better blood glucose control and lower T2DM complications. The related clinical, personal, and economic burden on people with T2DM and their carers and family will be reduced. People with T2DM will be cared for in line with the best available scientific evidence and in the same manner regardless of where or by which ayurvedic practitioner they are treated. Given that T2DM is a global concern, the clinical guideline will be of interest in other countries, particularly in neighboring South Asian nations and in countries with South Asian ethnic minorities who often rely on ayurvedic treatments.^[40,41]^

Health policymakers and managers will benefit from the availability of an effective solution to manage T2DM by ayurvedic practitioners. The related economic burden on the health system and economy will be reduced. The clinical guideline may improve the efficiency of healthcare through standardized care, providing better value for money. In the case of ayurvedic medicines of no, minimal, or questionable value, they will benefit from the identified disinvestment opportunities, cost savings, and opportunities for redirecting the resources (from ineffective to effective ayurvedic medicines). The provision of evidence-based healthcare and reduction in unacceptable variations in ayurvedic clinical practice will send messages of commitment to excellence and quality, thus building people’s confidence in the health system and improving the public image.
